## Abstract

**Background:**

Dose escalation of SBRT for locally advanced pancreatic cancer patients had been reported in several studies in one or three fractions, and phase I protocol was developed to investigate the maximum tolerated dose with CyberKnife for locally advanced unresectable pancreatic cancer patients in five fractions.

**Methods:**

The study is designed as a mono-center phase I study. The primary endpoint is to determine the maximum tolerated dose by frequency of III/IV GI (gastrointestinal) toxicity. Adverse events (AE) according to Common Toxicity Criteria (CTC) version 4. Doses of 7 Gy, 7.5 Gy, 8 Gy, 8.5 Gy, 9 Gy, 9.5Gy x 5 respectively would be delivered while meeting with normal tissue constraints. A minimum of three patients will be included for each dosage level. And an interval is 4 weeks from the first patient treatment to the next patient treatment at each dose level. The maximal tolerated dose will be defined as the dose for which at least two patients in three, or at least three patients in nine, will present with a limiting toxicity.

**Discussion:**

Since the dose and fractions of SBRT treatment for locally advanced pancreatic cancer patients are still unknown, we propose to conduct a Phase I study determining the maximum tolerated dose of CyberKnife SBRT for the treatment of locally advanced pancreatic tumor based on a 5 fractions treatment regimen. This trial protocol has been approved by the Ethics committee of Changhai hospital. The ethics number is 2016-030-01.

**Trial registration:**

Clinical trials number: NCT02716207.

Date of registration: 20 March 2016.

## Background

Pancreatic cancer is the fourth-leading cause of cancer-related death in the world. It is characterized by metastatic spread and local failure and seldom detected in its earlier stages. For locally advanced stage pancreatic cancer, the complete surgical removal is hard to achieve.

Stereotactic body radiotherapy (SBRT) with CyberKnife for locally advanced unresectable pancreatic cancer is a relatively new treatment option made available because of significant improvements in diagnostic imaging and radiation delivery techniques. Different from the conventional radiotherapy, radiation dose is delivered in fewer fractions and higher fractional doses in SBRT. Gurka [1] reported that 14 patients received SBRT with prescription dose of 25 Gy in five fractions with BED (biologically equivalent doses) of α/β = 10 in correspondence to 37.5Gy. Grade 1 to 2 gastrointestinal toxicity (no grade 3 or 4 radiation-related toxicities) was observed 2 weeks after treatment. Two patients had a partial response, and 12 patients were with stable diseases. In the previous dose escalation study, a single fraction upto15 Gy, 20 Gy, 25 Gywhich is an equivalent BED_10_ to 37.5Gy,60Gy,87.5Gy respectively is recommended by Koong AC [2] and his team. Even though the local control rate is 100%, the follow up is short and the sample size of 15 patients is relatively small. Moreover, the late toxicity is not investigated. And with single fraction scheme, higher late GI toxicities were reported [2–4]. In the meanwhile, investigators [5, 6] from South Korea examined that a Dmax of 35Gy and 38Gy in 3 fractions (BED_10_ to75.8Gy and 86.1Gy) of SBRT correlated with a 5 and 10% rate of grade 3 of gastroduodenal toxicity for abdominal malignant tumor, respectively.

Chuong [7] used 5 fractions to potentially decrease the risk of late normal tissue injury compared with 1 to 3 fractions commonly used in other institutions. Assuming α/β = 3, the EQD2 = nd*(d + α/β/2 + α/β) delivered to normal tissue in this study (using a mean 36.4 Gy in 5 fractions to the high dose PTV) was 75Gy, which is lower than the mean EQD2 from other series, the corresponding values from Boston and Stanford were 92.2Gy (mean, 32.96 Gy in 3 fractions) and 140Gy (mean, 25Gy in 1 fraction), respectively [8, 9]. And a relatively lower incidence of grade ≥3 late adverse effects (5.3% VS 9%) was observed.

## Methods and design

### Study design

The study is designed as a mono-center phase I study to evaluate the maximum tolerated dose for locally advanced unresectable pancreatic cancer treated with CyberKnife SBRT.

### Primary endpoint

To determine the maximum tolerated dose.

### Secondary endpoints

To assess the pain intensity by NRS scores.To assess acute and late toxicities following CyberKnife SBRT.Response rate by RECIST criteria.Relapse-free survival (RFS) and overall survival (OS).

### Inclusion criteria

Locally advanced unresectable pancreatic adenocarcinoma which is proved by biopsy.

A life expectancy of >3 months

KPS ≥70

Tumor size <5 cm

Tumor location: head of pancreas

Age of 18–75 years old

Patients must be able to undergo contrast enhanced CT for planning

Absolute neutrophil count ≥ 1,5 × 10^9^cells/L

Leukocyte count ≥ 3.5 × 10^9^cells/L

Platelets ≥ 70 × 10^9^cells/L

Hemoglobin ≥ 8.0 g/dl

Albumin >2.5 g/dL

Total bilirubin < 3 mg/dL

Creatinine < 2.0 mg/dL

INR < 2 (0.9–1.1)

AST < 2.5 × ULN (Upper Limit of Normal) (0–64U/L)

ALT < 2.5 × ULN (0–64U/L).

Both men and women and members of all races and ethnic groups are eligible for this study.

Ability of the research subject or authorized legal representative to understand and the willingness to sign a written informed consent document.

Tumor markers and lab test should be done less than 1 week before recruitment.

### Exclusion criteria

Prior surgery, chemotherapy or radiation for pancreatic tumor.

Prior radiotherapy of the upper abdomen, evidence of metastatic disease such as nodal or distant metastases by abdomen CT and chest CT.

Contraindication to receiving radiotherapy.

Distance between GTV (lesion) and luminal structures (including liver, stomach, duodenum, small or large bowel) is less than 5 mm.

Women who are pregnant or participation in another clinical treatment trial while on study.

Patients in whom fiducial implantation were not possible.

### Radiation treatment planning

SBRT will be delivered on CyberKnife with Synchrony Respiratory Tracking system. The tumor will be tracked with implanted fiducial markers by Fiducial Tracking System. Treatment will be delivered in 5 fractions within 1 to 2 weeks at the discretion of the investigator.

A body fixation (vacuum-bag) will be used in immobilizing the body, the arms (both arms are along the body) and the legs.

Dose will be administered according to the following recommended schedule: Doses of 7 Gy, 7.5 Gy, 8 Gy, 8.5 Gy, 9 Gy, 9.5Gy x 5 with BED_10_ in correspondence to 59.5 Gy, 65.6 Gy, 72 Gy, 78.6 Gy, 85.5 Gy, 92.6 Gy respectively would be delivered while meeting with normal tissue constraints (Table 1). A minimum of three patients will be included for each dosage level. And an interval is 4 weeks from the first patient treatment to the next patient treatment at each dose level. In case patient presents III/IV GI toxicity, three additional patients will be included at the same dose level.

**Table 1 Tab1:** Diagram of dose escalation

Level	Dose (Gy)	Fractions	Total (Gy)
1	7	5	35
2	7.5	5	37.5
3	8	5	40
4	8.5	5	42.5
5	9	5	45
6	9.5	5	47.5

The maximal tolerated dose will be defined as the dose for which at least patients in 3, or at least three patients in 9, will present with a limiting toxicity.

Margins: The Gross Tumor Volume (GTV) is defined as the visible tumor based on contrast enhanced CT acquired on portal-venous phase. The clinical target volume (CTV) equals the GTV. The planning target volume (PTV) was usually defined as the region of 2–5 mm outside of CTV. When tumor is adjacent to critical organs especially duodenum, we choose to avoid expanding PTV outside of CTV in this direction.

An individualized treatment plan will be developed based on tumor geometry and location. At least 90% volume of PTV should be covered by the prescription dose. The prescription isodose line was limited to 70–75% which will restrict tumor Dmax. e. If dose level violates the constraint of SBRT, the patient will be considered as ineligible for this trial (Table 2).

**Table 2 Tab2:** Critical structures and constraints

Organ	Dose limits (5 fractions)	Volume
Liver	17.5 Gy	≥700 cc spared
Kidney	<12 Gy	Dmean
Spinal cord	23 Gy	0.35 cc
Spinal cord	27Gy	Dmax
Duodenum	18Gy	5 cc
Duodenum	12Gy	10 cc
Small bowel	19.5Gy	5 cc
Stomach	18Gy	10 cc
Esophagus	19.5Gy	5 cc
Large Bowel	25Gy	20 cc

Based on The Report of AAPM (American Association of Physicists in Medicine) Task Group 101

Fiducial (Soft tissue gold markers, 0.9 × 3 mm, CIVCO, Orange City, lowa 51041 USA) implantation will be done under endoscopic ultrasonography (EUS) guidance. The recommended number of implanted fiducials is 3 (at least 1) which is preferable to be close to, but not in the tumor. A time-period of 4–7 days between implantation and treatment planning CT-scan is recommended.

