### Duration of intervention and evaluation

The duration of treatment will be 1 to 2 weeks. It is delivered every day and 5 times a week. In case of machine breakdown, it will be extended to 2 weeks. The follow-up period will be for 1 year following completion of therapy. The trial is planned to begin on September 2016. There cruitment period of the entire study (27 patients) will take approximately 1 year. Acute and late toxicity according to CTCAE 4.0will be evaluated. Triple phase enhanced abdomen CT scan (<4 weeks), physical examination and lab test will be assessed at 1, 3, 6, 9, 12 months after completion of treatment.

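### As printed, a dose level cleared on 0 of 3 is never enlarged, so the reported dose may well rest on three patients although 27 are planned

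*Protocol article*

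**What the plan says.** Radiation treatment planning lists six levels, 7 to 9.5 Gy in five fractions, and sets the cohort size: "A minimum of three patients will be included for each dosage level". The only stated reason to add patients follows: "In case patient presents III/IV GI toxicity, three additional patients will be included at the same dose level".

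The MTD is stated twice. The Methods part of the Abstract has "The maximal tolerated dose will be defined as the dose for which at least two patients in three, or at least three patients in nine" with a limiting toxicity. Radiation treatment planning has "The maximal tolerated dose will be defined as the dose for which at least patients in 3, or at least three patients in 9", where the first count is missing. Both wordings attach the term to the level at which the toxicity count is reached. Neither says what happens after two toxicities in six.

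The total appears once, under Duration of intervention and evaluation, as the recruitment "period of the entire study (27 patients) will take approximately 1 year". It is not derived, and no use is named for patients whom the escalation does not need.

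**The concern.** Enlargement is tied to toxicity alone. A level with 0 of 3 is left behind, and the printed rule does not return to it if the next level proves limiting or if it is the last level. The level reported as tolerated may then be supported by three patients. That is thin evidence for the trial's only primary endpoint: a level with a true grade III/IV GI rate of 30% shows 0 of 3 with probability 0.7^3 = 34%, and one with a true rate of 40% with probability 0.6^3 = 22%. Meanwhile the planned total exceeds the minimum of 6 x 3 = 18 by nine patients, so a larger group at the reported level may often be affordable within the stated size.

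**Working it through.** **The planned 27.** It cannot be reproduced from stated inputs. Six levels need at least 6 x 3 = 18 and at most 6 x 9 = 54 patients; 27 is 18 plus three further cohorts of three.

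**Precision.** For 0 of n, the exact one-sided 95% upper bound is 1 - 0.05^(1/n): 63.2% for n = 3, 39.3% for n = 6, 28.3% for n = 9. One toxicity in six gives 58%.

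**Readings of the 3-6-9 rule.** In each, 0/3 clears the level, 1/3 adds three, and 2/3 or more is limiting.
- R1: two or more in six is limiting.
- R2: three are needed in six.
- R3: two in six goes on to nine, and three in nine is limiting.

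**Probabilities at a level with toxicity rate p.**
- Cleared on three: (1-p)^3.
- Limiting on three: 3p^2(1-p) + p^3.
- Cleared on six, R1 and R3: 3p(1-p)^5.
- Cleared on six, R2: 3p(1-p)^5 + 9p^2(1-p)^4.
- Cleared on nine, R3 only: 9p^2(1-p)^7.

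Example with p = 10% under R1: 0.729 cleared on three and 0.3 x 0.9^5 = 0.177 cleared on six, so 0.729/0.906 = 80% of clearances rest on three patients.

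**Across levels.** Let C_k be the chance that level k is cleared.
- Highest cleared level has three patients: sum over k of [C_1...C_(k-1)] x (1-p_k)^3 x (1 - C_(k+1)), with the last factor equal to 1 at level 6, divided by C_1.
- Literal wording (the level that meets the toxicity rule, or the top level if none does): sum over k of [C_1...C_(k-1)] x P(limiting on three at level k), plus [C_1...C_5] x (1-p_6)^3.

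**Toxicity curves, all assumed.** The article gives no rates for its own levels.
- I: 5, 10, 15, 20, 25, 30%.
- II: 5, 10, 20, 30, 40, 50%.
- III and IV: logistic in biologically effective dose, D(1 + (D/n)/(alpha/beta)), through the Background's rates. There, maximum doses of 35 and 38 Gy in three fractions "correlated with a 5 and 10% rate of grade 3 of gastroduodenal toxicity for abdominal malignant tumor, respectively". These doses convert to 43.7 and 47.6 Gy in five fractions at alpha/beta 3, and to 41.5 and 45.2 Gy at alpha/beta 10. If the GI organ maximum is set equal to the prescription, the levels have 1.2, 1.7, 2.6, 4.0, 6.3, 9.9% (III, alpha/beta 3) or 1.6, 2.4, 3.8, 6.1, 9.6, 15.1% (IV, alpha/beta 10).

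**Results (exact enumeration).** The last two columns fill the highest cleared level to six.

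| Curve | Reading | Highest cleared level has n=3 | Literal wording, n=3 | Mean N | N>27 | Mean N, filled to six | N>27, filled to six |
|---|---|---|---|---|---|---|---|
| I | R1 | 75% | 41% | 17.0 | 1.2% | 19.2 | 3.1% |
| I | R2 | 58% | 63% | 20.3 | 5.5% | 22.0 | 9.6% |
| I | R3 | 67% | 52% | 20.4 | 10.9% | 22.4 | 16.5% |
| II | R1 | 75% | 43% | 15.1 | 0.4% | 17.3 | 1.1% |
| II | R2 | 55% | 69% | 18.2 | 3.6% | 19.8 | 5.6% |
| II | R3 | 67% | 53% | 17.9 | 4.9% | 19.9 | 7.4% |
| III | R1-R3 | 76-82% | 73-76% | 19.6-20.2 | 0.1-0.9% | 22.1-22.5 | 0.4-2.1% |
| IV | R1-R3 | 68-78% | 62-68% | 19.9-21.0 | 0.3-2.7% | 22.2-23.2 | 1.0-5.3% |

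**Wider assumptions.** With flat rates from 0 to 30%, further rising curves up to 10-60%, and readings in which one toxicity in three always leads towards nine, mean unused enrolment runs from about 3 to 19 of the 27, and 27 is exceeded in up to 32% of trials.

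**The case against.** Four objections have force.

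- **Definition.** Read literally, the declared MTD is the level that meets the toxicity rule, not one cleared on 0 of 3. A reader might infer that the reported dose will usually rest on three patients. On the literal wording this is close to a coin toss for curve I (41-63%), so the text does not support it without the assumption that the cleared level is the one reported. The point survives in weaker form, because a trial that ends at the top level, or reports the level below the limiting one, can still rest on three.
- **Unused patients.** A reader might infer that a fixed block of some six to ten patients is never used. That count depends on assumed rates and on an incomplete rule. Moreover, a minimum of three permits more, and a condensed article may omit a confirmation cohort held in the full protocol. What stands is that the article prints the cohort size, the trigger and the total, and the printed rule gives no other occasion to enlarge a level.
- **Cited rates.** A reader might infer that the Background's 5% and 10% make this the likely path. They relate to maximum dose in a three-fraction series. The conversion sets organ maximum equal to prescription, although the exclusion criteria require distance from luminal organs, Table 2 sets GI dose limits, and the prescription is to the 70-75% isodose. The Discussion itself calls the linear-quadratic model insufficient for hypofractionated treatment. Curves III and IV are illustrations.
- **Comparison with the limiting rate.** The 63% bound exceeds three in nine (33%) but lies below the Abstract's other criterion, two in three (67%). Calling it twice the limiting rate would be selective.

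**Conclusion.** The concern holds as a modest and inexpensive improvement. As printed, only a grade III/IV GI toxicity enlarges a level, so a level with 0 of 3 is passed and stays at three even if it ends as the highest level not found limiting. Under the four assumed curves and three readings, that level has three patients in about 55-82% of trials; on the literal MTD wording the reported level has three in about 41-76%. Neither range can be narrowed until the two MTD statements are reconciled. Mean enrolment of about 15-21 suggests room within 27 on these curves, but not with certainty. What does not depend on the curves is the precision: an upper bound of 63% after 0 of 3, against 39% after 0 of 6.

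**What to change.** First, reconcile the MTD wording in the Abstract and in Radiation treatment planning, including the missing count and the outcome after two toxicities in six, so that it is clear which level is declared. Which rule to adopt is for the sponsor.

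Then add: a level not found limiting is reported as tolerated only after at least six patients have been treated there, drawn from those remaining of the planned 27 (more only if patients remain) and assessed under the reconciled toxicity rule; the GI toxicity rate at that level is reported with an exact confidence interval. Where 27 is reached first, only the exact interval is reported.

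Six fits the stated size in most trials: on the curves above, mean enrolment becomes about 17-23 and 27 is passed in about 0.4-17% of trials. A fixed target of nine fits less well. It passes 27 in up to about 30% of trials on these curves, and averages up to 27.6 patients when one toxicity in three always leads towards nine.

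The cost is usually three more patients at the reported level, plus accrual time. If the article's 4-week interval applies between successive patients, three more could take up to 3 x 4 = 12 weeks, against a recruitment period of about one year. The gain to 39% applies only if no toxicity appears; with one in six the bound is 58%.

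### The expansion rule adds three patients at dose levels that already meet the MTD criterion, and the dose labelled as the MTD is the one that meets it

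*Protocol article*

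**What the plan says.** The determination of the MTD is the only primary endpoint: "To determine the maximum tolerated dose" (Primary endpoint). The abstract's Methods paragraph ties it to the frequency of grade III/IV GI toxicity.

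The rule itself is in Radiation treatment planning:

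- Cohort size: "A minimum of three patients will be included for each dosage level".
- Expansion: "In case patient presents III/IV GI toxicity, three additional patients will be included at the same dose level".
- MTD: the dose for which "at least patients in 3, or at least three patients in 9, will present with a limiting toxicity". The count in the first limb is missing. The abstract has it: "at least two patients in three, or at least three patients in nine, will present with a limiting toxicity".

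Table 1, titled "Diagram of dose escalation", lists six dose levels from 35 to 47.5 Gy in steps of 2.5 Gy and no decisions. Duration of intervention and evaluation gives the planned size: "entire study (27 patients) will take approximately 1 year".

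**The concern.** The expansion sentence is triggered by any grade III/IV GI toxicity and makes no exception for a level whose fate is settled. The MTD definition settles a level at two or more in three. At such a level both sentences apply and point in different directions: one says the dose is limiting, the other says to treat three more patients at it. The same happens at three or more in six, because those toxicities cannot be undone by adding patients.

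The second problem is the label. Read as printed, the dose that reaches the toxicity criterion is the maximal tolerated dose. That is the dose at which too many patients had severe toxicity, not the highest dose that patients tolerated.

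Patients could be exposed without need to a dose already found limiting, and the primary result could be reported one level too high.

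**Working it through.** **Inputs.** Cohorts of three, three more after a toxicity, and limits of at least 2/3 or at least 3/9 (Radiation treatment planning, with the abstract for the missing count). Limiting toxicity is taken to be grade III/IV GI toxicity, as in the abstract. The article states no toxicity rate, so true rates p of 10, 20, 30 and 40% are assumed. Patients are treated as independent.

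**1. Where the two sentences collide.**

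- At least two in three: P = 3p²(1−p) + p³. At 30%: 3 × 0.09 × 0.7 + 0.027 = 0.216.
- One in three, then at least three in six: P = 3p(1−p)² × [3p²(1−p) + p³]. At 30%: 0.441 × 0.216 = 0.095.

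| Assumed rate | 10% | 20% | 30% | 40% |
|---|---|---|---|---|
| At least 2/3 | 0.028 | 0.104 | 0.216 | 0.352 |
| 1/3, then at least 3/6 | 0.007 | 0.040 | 0.095 | 0.152 |
| Either | 0.035 | 0.144 | 0.311 | 0.504 |

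Each such level takes at least three patients who cannot help to decide it. The expected excess per level opened is at least three times the last row: 0.10, 0.43, 0.93 and 1.51 patients.

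**2. A level that meets one limb and fails the other.** Take exactly two in three, with P = 3p²(1−p) = 0.027, 0.096, 0.189 and 0.288. If the level is expanded to nine without further toxicity, with probability (1−p)⁶ = 0.531, 0.262, 0.118 and 0.047, it ends at 2/9. It met the limit at three patients and does not meet 3/9. The joint probability is 0.014, 0.025, 0.022 and 0.013. This is uncommon, but the text gives no answer when it happens.

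**3. The dose that is named.** By the printed definition, the MTD is a level where at least 2/3 (67%) or 3/9 (33%) of patients had a limiting toxicity. The level below it, the highest that did not meet the criterion, is 2.5 Gy lower in total (Table 1). From the article's own BED10 values the gap is 65.6 − 59.5 = 6.1 Gy at the bottom of the range and 92.6 − 85.5 = 7.1 Gy at the top.

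**4. The path from three to six to nine.** The expansion sentence has no cap. Applied again after each new toxicity, it takes 1/3 to six and 2/6 to nine, and lets 1/6 escalate. The alternative is to take every expanded level to nine. With a stop at 2/3 in both cases, the chance of meeting the criterion is:

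- Only 2/6 goes to nine: P(at least 2/3) + P(1/3, then at least 3/6) + P(1/3, then 2/6) × [1 − (1−p)³]. At 30%: 0.216 + 0.095 + 0.194 × 0.657 = 0.439. Across the four rates: 0.051, 0.216, 0.439, 0.650.
- Every expanded level goes to nine: 0.056, 0.236, 0.472, 0.683.
- Difference: 0.005, 0.020, 0.033, 0.033.

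**5. Planned size.** 6 × 3 = 18, and 27 − 18 = 9, which is three added cohorts. That fits any reading, so it does not settle the rule.

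**The case against.** **The rule can be completed by a sensible reader.** This largely stands for the middle of the rule. A reader might infer that 2/6 has no printed action, that such a level is free to escalate, or that the chance of stopping at a 30% level is open from 0.31 (2/6 escalates) to 0.51 (2/6 stops). The text does not support this. Reaching 2/6 from 1/3 means that a further patient had a toxicity, and the uncapped sentence then calls for three more, giving the nine that the criterion uses. Escalating at 2/6 would leave the limit at nine without use, and no printed criterion stops a level at 2/6. The unstated rows at six are mostly detail that an article may leave to the full protocol.

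**The missing count is a misprint.** This stands. The abstract settles it and no other value is printed, so it does not leave the criterion undefined.

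**At two in three the MTD is already met, so nobody would expand.** This is the likely intention, but it has to be supplied by the reader against a sentence without exceptions. It is true that the effect on the decision is small. Expanding even at 2/3, going on to nine and stopping once three toxicities are reached gives 0.211, 0.449 and 0.670 at 20, 30 and 40%, within about 0.02 of the repeat-after-toxicity completion. The cost falls on patients: at 30% that version treats 6.2 patients per level on average, against 5.4 when 2/3 stops and every other expanded level goes to nine.

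**The label may be a matter of convention.** The term can be used for the dose at which escalation stops. That would be harmless if a recommended dose were named separately, but the article names none.

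**Conclusion.** The point holds in a limited form and should be fixed. Two statements are wrong as written: the expansion step has no exception for levels that have met, or are certain to meet, the criterion; and the definition names the limiting level as the maximal tolerated dose.

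At assumed true rates of 10 to 40%, the first conflict arises at 2/3 or more with probability 0.03 to 0.35 per level opened, or 0.035 to 0.504 when three or more in six is included. These are chances of reaching a state where the sentences disagree, not of a wrong decision. The second shifts the reported dose by one level, 2.5 Gy in total, whenever the definition is followed as printed and a level below exists.

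The incomplete path from six to nine is secondary: the completions that reach nine differ by at most about 0.03. The documents do not show that the site would over-treat or report the wrong dose, only that the printed text tells it to. Because this rule produces the only primary endpoint, and the article chose to print it, condensation does not excuse sentences that conflict.

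**What to change.** Amend the protocol before the first expansion:

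1. Limit the added cohort of three to levels that have not met the criterion.
2. Print the decisions in one table:

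| Toxicities / treated | Action |
|---|---|
| 0/3 | escalate |
| 1/3 | add three |
| 2/3 or more | stop |
| 1/6 | escalate |
| 2/6 | add three |
| 3/6 or more | stop |
| 2/9 or fewer | escalate |
| 3/9 or more | stop |

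3. Restore the word *two* in the MTD sentence of Radiation treatment planning.
4. State that the reported MTD is the highest level that did not meet the criterion. If the stopping level is meant, label it the limiting dose and name the recommended dose separately.

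The cost is one word, one limiting clause, one short table and one sentence. It needs no change of dose levels and no extra patients; compared with the literal text it spares some.
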